#### Physical activity program

Participants will be advised to perform at least 150 min/week of moderate PA as per the PA recommendations for older people [70]. Where walking is a suitable and acceptable option to the participant, this will be a primary PA recommendation. Examples will be given on how this can be achieved. The program will be individualized based on the CHAMPS and SCI data, and the person’s interests. Activities prescribed will take into account health problems or other limitations, and participants will be instructed to start slowly and progress gradually taking eight weeks to reach the target amount and intensity. Participants will be encouraged to achieve the 150 min/week by completing 3 x 50 minutes sessions (most PA classes range between 45–60 minutes). In previous studies with middle-aged and older women using this format, we have demonstrated good retention, adherence and improvements in cardiovascular fitness and blood pressure [71]. Participants who already perform 150min/week of PA will be encouraged to increase their PA by adding one 50-minute session. Some participants might choose to complete activities in community centers. This home-based PA program was successful in maintaining retention, increasing PA and improving cognition in participants with MCI and those with subjective memory complaints [24]. Modifications have been made to the PA program and other components of the intervention to enhance motivation and to maintain PA over the 24-month intervention.

In order to maintain standardization of the physical activity programs one CI will monitor the programs prescribed by the PA RA. The PA program will include instructions on how to read the program, complete the activities, record their sessions, and exercise safely. Participants will be given a simple diary to record their PA. The diaries, once completed, will be mailed back to the PA RA at the end of each month.

Adherence during the intervention will be calculated from the number of sessions completed and recorded on the exercise diaries. This will be expressed as a percentage of the number of sessions completed relative to the number of sessions prescribed.

#### Behavioral intervention

Participants will receive the same educational material and recommendations for a healthy lifestyle as the control group. In addition they will receive a manual containing the PA program and the behavioral intervention (BI). The intervention program will be based on the Stages of Change model modified for PA [58], which has been shown to be effective in increasing and maintaining PA in middle-aged and older women [71]. This approach is based on the development of self-efficacy (the belief that one has the ability to perform a task) to promote change [72]. It will also draw on another key component of social cognitive theory and behavior change self-regulation; the personal regulation of goal directed behavior or performance [72,73]. The BI program will aim to develop self-efficacy by promoting practical strategies to enhance both physical skills and self-regulation skills. We will use our previously successful strategies [71] with the addition of greater emphasis on identifying and setting goals, self-monitoring, giving relevant feedback, review of progress and identifying action steps to enhance self-regulation skills.

Strategies to increase adherence to the program will be discussed during the workshop and worksheets will be included in a manual. During the 24-month trial, the PA RA will mail newsletters at regular intervals to participants, which contain additional motivational information. This will also be reinforced during the 18 telephone calls made at regular intervals. Participants will be contacted by telephone for a standardized and structured 15-minute interview to monitor and give feedback on their progress and encourage their continuing adherence. In addition pedometers will be given to the participants for the duration of the study and midway through each 6-month period they will be asked to record their daily steps for 4 weeks while trying to reach a personalized target. Pedometer-based interventions have been shown to be an effective way to help maintain PA in older adults [74]. Participants will also be given a PA report after their follow-up assessments. Giving feedback about progress and increasing participants’ perceived benefits of being more physically active has been shown to increase program adherence [75].

#### Content and program evaluation

At the end of each follow-up visit, the intervention group participants will be asked to complete a brief interview questionnaire on the content and processes of the program including how easy the program was to understand and follow, and any barriers that were encountered.

#### Control group

Control group (usual care) participants will receive educational material and recommendations for a healthy lifestyle (other than PA). Participants will be contacted by telephone at the same frequency as the intervention group to ensure that the control and intervention group have similar treatment except for the actual intervention. Conversation for this group will be limited to their general health and will not include discussion about PA. At the end of each follow-up visit, control group participants will be asked to complete a brief interview questionnaire related to their involvement in the study. At the conclusion of the study, these participants will be offered the opportunity to attend an educational session on PA.

### Statistical methods

Participants who drop out during the trial will be invited to return for the follow-up assessments. We will use imputation by chain equations (ICE) to estimate possible missing outcomes in an intention-to-treat analysis (primary analysis). A complete-case analysis will also be conducted, which includes participants with valid data at all time points. We will use multilevel regression models to take into account repeated measures and intra-individual variability (mixed models). These models will be adjusted for confounding should the randomization produce unbalanced groups.

The volumetric change in WMH white matter load at 24 months and the modified WMH change score will be assessed using an independent 2-sample *t*-test or Mann–Whitney *U* test, depending on whether the data satisfies assumptions of normality. The modified WMH change score may also be collapsed into a smaller number of categories and assessed using a chi-square test. General linear models will then be used to estimate treatment effects after correcting for initial WMH severity, age, depression, MTA, cognition and VRF. The predictive contribution of these confounding variables will also be investigated. Model assumptions of normality and constant variance will be checked and data will be transformed if required. A multiple imputation method will be applied to replace missing observation values during the follow-up for key analysis variables if necessary. The change in secondary outcomes, cognition, fitness, depression, quality of life and functional levels, between baseline and 24 months and between groups will be analyzed. General linear models will be fitted for each outcome separately and known confounding variables will also be included in this analysis. Frequency counts and chi square analyses will be used to determine the distribution of subjects for retention in the study and demographic data. Changes in PA, fitness, blood pressure, body weight, body composition and socio-psychological variables will be analyzed across the entire follow-up period, using repeated measures mixed model analysis. Amyloid status is another important explanatory variable in the progression of WMH. This will be incorporated into the general linear model described in the analysis of the primary outcome. The interaction effect between amyloid status and treatment will also be included in the model to assess whether amyloid status influences patient response to treatment.

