**Methods/design:**

This single-blind randomized controlled trial (RCT) is offered to 156 participants, aged 60 and older, in the Melbourne arm of the Australian Imaging Biomarkers and Lifestyle Flagship Study of Aging (AIBL). Participants must have SMC with or without MCI and at least one VRF. The PA intervention is a modification of the intervention previously trialed in older adults with SMC and MCI (Fitness for the Ageing Brain Study). It comprises 24 months of moderate, home-based PA (150 minutes per week) and a behavioral intervention package. The primary outcome measure will be change in WMH after 24 months on MRI. Cognition, quality of life, functional fitness, level of physical activity, plasma biomarkers for cerebrovascular disease and amyloid positron emission tomography (PET) imaging comprise secondary measures.

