##### Visual assessment of white matter disease progression and medial temporal lobe atrophy

White matter hyperintensities (WMH) at baseline will be rated using the Scheltens scale (range, 0 to 84 points) [62]. Visual assessment of progressive white matter disease will be performed using the modified Rotterdam Progression Scale [63]. This score ranges from 0 to 9, scoring stable (0) or increase (1) in 9 regions. Intra and inter rater reliability for these methods will be assessed and have previously been shown to be high [64]. Medial Temporal lobe Atrophy (MTA) has been linked to both progressive white matter disease [65] and cognitive decline [66] in MCI participants. Visual assessment of the medial temporal lobes will be performed on coronal T1 images from the volume set according to the 5 point (0–4) Scheltens scale from the average score of the left and right sides [67].

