##### Volumetric MRI analysis

Volumetric analysis of the white matter lesions will be performed at a laboratory equipped with FSL (http://www.fmrib.ox.ac.uk/fsl) and Analyze (http://www.analyzedirect.com) software packages. A semi-automated threshold region of interest (ROI) based approach to white matter lesions will be used. All ROIs selected will be reviewed by a neuro-radiologist to confirm accurate identification of lesions and accurate identification of contours of lesions. The volume of the lesions will be summed to give a total lesion volume or total WMH. This will be standardized to the whole brain volume to control for individual differences in brain size. A fully automated measure of white matter lesions will be undertaken using published automated image processing algorithms [68] and compared with the results of the semi-automated supervised technique. Similarly, volumetric analysis of the medial temporal lobe will be performed manually and in an automated fashion. The manual segmentation will be performed by identifying the contours of the hippocampus on coronal T1 weighted images, employing well defined anatomical landmarks [69]. This will be compared to an automated technique. Hippocampal volumes will be standardized to the whole brain volume to control for individual differences in brain size.

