#### Sample size and power calculation

The primary outcome of interest in this study is change of WMH on follow-up MRI after two years. To our knowledge there is no study having investigated the effect of PA on progression of WMH in older adults with SMC and MCI. However in a recent RCT, Richard et al. [76] compared WMH progression in 123 participants with AD who received either vascular care or standard care over a two-year period. Vascular care was defined as treating vascular risk factors as good as possible. Scans were analyzed and WMH at baseline were rated using visual semi-quantitative rating scales. Progression of WMH was measured using the modified while matter lesion (WML) change score (range 0 to 9) [63]. After two years participants in the vascular care group had less progression of WMH compared to the standard care group (1.4 versus 2.3, p = 0.03) with a significant linear trend (p=0.009). We hypothesize that in our participants the effect of the PA program on WMH would be similar to that of vascular care intervention. Based on the WML change, with a medium effect size of 0.5, 80% statistical power and a two-sided alpha error level of 0.05, we therefore would need 65 participants per group. Allowing for 15% loss to follow-up we will need 76.5 participants per group. We will recruit 78 participants per group for a total of 156 participants.

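### The primary outcome, change in WMH, is not tied to one measure: lesion volume and the 0 to 9 visual score are both tested with no stated order, success rule or adjustment, and only the score is powered

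*Protocol article*

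**What the plan says.** The outcome is stated twice without a measure. The Abstract (Methods/design) says "The primary outcome measure will be change in WMH after 24 months on MRI", and Sample size and power calculation says "The primary outcome of interest in this study is change of WMH on follow-up MRI after two years".

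The imaging sections then define two ways of measuring that change:

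- **Visual score.** "Visual assessment of progressive white matter disease will be performed using the modified Rotterdam Progression Scale". Each of nine regions scores 0 (stable) or 1 (increase), so the range is 0 to 9.
- **Lesion volume.** "The volume of the lesions will be summed to give a total lesion volume or total WMH". This is standardized to whole brain volume.

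Statistical methods takes both together: "The volumetric change in WMH white matter load at 24 months and the modified WMH change score will be assessed", each by a t-test or a Mann–Whitney test depending on normality. It adds a further option for the score: "The modified WMH change score may also be collapsed into a smaller number of categories and assessed using a chi-square test". Covariate-adjusted general linear models follow. When amyloid status is introduced later in the same paragraph, the text looks back at those models: "This will be incorporated into the general linear model described in the analysis of the primary outcome".

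The sample size calculation takes its precedent from a two-year trial of vascular care in Alzheimer's disease that used the 0 to 9 score (1.4 versus 2.3). It assumes an effect size of 0.5 on that score. No effect size, standard deviation or power is given for volume.

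**The concern.** The two measures differ in kind. One counts regions rated as worse; the other sums lesion volume. They can disagree: growth concentrated in one region can raise volume a good deal and the score by a single point.

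A trial with one primary question needs one variable that answers it, or a rule for combining several. Here two variables sit inside the primary analysis with neither. Two things are at stake. First, if one measure is significant and the other is not, the protocol does not say what the trial has shown. Second, nothing in the text prevents the more favourable measure from being presented as the primary result afterwards. If that happened, the nominal 5% error rate would not describe the claim being made.

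**Working it through.** **Step 1. Is one of the measures placed elsewhere as secondary?** The Abstract lists cognition, quality of life, fitness, activity level, plasma markers and amyloid PET as secondary. The secondary objectives at the end of Background and the secondary outcomes in Statistical methods are similar. No WMH measure is in any of the three lists. Both measures therefore remain in what the text itself calls the analysis of the primary outcome.

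**Step 2. Reproduce the sample size.** Inputs from Sample size and power calculation: d = 0.5, power 80%, two-sided alpha 0.05, 15% loss. Allocation is 1:1 (Randomization and blinding).

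- Normal approximation: n = 2(1.960 + 0.842)² / 0.5² = 62.8, so 63 per group.
- Exact t-test: 63.8, so 64 per group.
- The stated 65 is consistent with both. Power at 65 per group is 80.8% (t-test) to 81.3% (normal).
- Loss: 65 / 0.85 = 76.5, as stated; 78 are recruited per group.

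The arithmetic is sound, but it concerns the score only.

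**Step 3. False-positive risk if either measure could count.** Assume each is tested at two-sided 0.05 and there is no effect on either. Then

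risk = 1 − P(|Z₁| < 1.96 and |Z₂| < 1.96),

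with Z₁ and Z₂ bivariate normal with correlation ρ. At ρ = 0 this is 1 − 0.95² = 9.75%. The document gives no value of ρ, so a range is shown:

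| Assumed ρ | Risk of at least one false positive |
|---|---|
| 0 | 9.75% |
| 0.3 | 9.5% |
| 0.5 | 9.1% |
| 0.7 | 8.35% |
| 0.8 | 7.8% |
| 0.9 | 7.0% |

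Both measures describe the same lesions on the same scans, so a clearly positive correlation is likely and the top of the range is the less plausible end. The optional chi-square test is not counted here.

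**Step 4. Cost of keeping both by splitting alpha.** At 0.025 each, and assuming d = 0.5 for each measure:

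- Evaluable per group: 77 (normal) to 78 (t-test).
- Recruited per group: 77 / 0.85 = 90.6, so 91; 78 / 0.85 = 91.8, so 92.
- Total: 182 to 184, against 156 planned.
- With the planned numbers (65 to 66 evaluable per group), power per measure falls to about 72% to 73%.

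**The case against.** The strongest reply is that the document names a single outcome, and that the sample size section moves straight from that outcome to the 0 to 9 score, which hints that the score is meant. Against this, Statistical methods lists volume first and ranks neither. A hint in one section does not settle what another leaves open.

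A second reply is that an analysis plan, not shown here, may set the error control. That would excuse the absence of a multiplicity procedure. It does not excuse leaving the primary measure unnamed, because that choice defines the trial's question and the sample size depends on it.

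Three stronger readings are tempting, and the document does not support them:

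- **That both tests are planned at 0.05, so the stated alpha is broken.** The value 0.05 appears once, in the sample size section. Using it for each test is the natural reading, but it is not written.
- **That success on either measure is the plan's rule.** There is no success rule. Requiring both, or treating volume as supportive, fits the text equally well. With both required, the error rate would not rise above 5%.
- **That fully automated volume is a third primary measure.** The sentence beginning "A fully automated measure of white matter lesions will be undertaken using published automated image processing algorithms" goes on to say that its results will be compared with the supervised semi-automated technique. It is already a method comparison, and Statistical methods gives it no separate test.

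It is also fair to say that the trial is presented as proof of concept. That softens the consequences of a modest rise in error, but not the need to know which measure answers the question.

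**Conclusion.** The concern holds in this form: the primary outcome is not fixed to one measure, two are tested in the primary analysis with no ranking or decision rule, and only one is powered. This rests on the text alone.

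The error rate of about 7% to 9.75% is conditional. It needs an either/or reading, 0.05 for each test, and an assumed correlation between 0.9 and 0. For two exact 5% tests with jointly normal statistics, 9.75% is the ceiling. What is established is that the primary result could be selected after the data are seen, not that the plan prescribes an inflated alpha. The sample size calculation is correct for the score.

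**What to change.** In the Abstract, Statistical methods and Sample size and power calculation:

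1. Name the modified Rotterdam change score at 24 months as the only primary outcome.
2. Fix one primary test for it in advance. Describe the chi-square on collapsed categories, and any other analysis of the score, as supportive.
3. Make the semi-automated volume change, standardized to whole brain volume, the first secondary outcome, tested at two-sided 0.05 only if the primary test is significant.

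The change is one of wording. The sample size stays at 65 evaluable and 78 recruited per group, 156 in total. The price is that an effect seen on volume alone could not be claimed as confirmatory.

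If the investigators intend volume as primary, the change is larger: the sample size section would need an effect size and a power justification for volume, and the document contains neither. Keeping both with a split alpha is possible, but at the cost shown in the working.

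### If the 0 to 9 WMH change score is collapsed to three or more categories, the optional chi-square test ignores their order; a trend or ordinal test should be named instead (minor)

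*Protocol article*

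**What the plan says.** The visual outcome is the modified Rotterdam Progression Scale. The section on visual assessment of white matter disease defines it: "This score ranges from 0 to 9, scoring stable (0) or increase (1) in 9 regions".

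Statistical methods first assigns this score, together with the volumetric change, to a two-sample t-test or a Mann–Whitney U test, "depending on whether the data satisfies assumptions of normality". It then adds: "The modified WMH change score may also be collapsed into a smaller number of categories and assessed using a chi-square test". The number of categories, the cut-points and the form of the chi-square test are not given. General linear models correcting for initial WMH severity and other covariates follow.

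The sample size section rests on this same score, "with a medium effect size of 0.5, 80% statistical power" and "a two-sided alpha error level of 0.05", and concludes that "we therefore would need 65 participants per group". Its reference is an earlier trial of vascular care: "After two years participants in the vascular care group had less progression of WMH compared to the standard care group", with mean scores of 1.4 and 2.3 (p = 0.03). For that trial the section also reports a linear trend with p = 0.009.

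**The concern.** The trial asks whether physical activity shifts participants towards fewer worsened regions. A Pearson chi-square test on a 2 × k table treats the k categories as unordered labels. It spreads its sensitivity over k − 1 degrees of freedom, and its alternative is any difference in category proportions, including more people at both extremes with no net change.

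Two things follow for three or more categories. A real shift to less progression is less likely to be detected than with an ordered test on the same table. And a significant result need not mean less progression. In a proof-of-concept trial, a chi-square p-value that disagrees with the main comparison for either reason would be hard to interpret. The reference trial's result was reported as a linear trend, which does use the order, but the plan for the collapsed score names no such test.

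**Working it through.** **1. The plan's own figure.** Inputs from the sample size section: standardized effect 0.5, two-sided alpha 0.05, power 80%.

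- Normal approximation: n = 2 × (1.960 + 0.842)² / 0.5² = 2 × 7.85 / 0.25 = 62.8, so 63 per group.
- Noncentral t: 63.8, so 64 per group.
- Allowing for Mann–Whitney efficiency: 63.8 / 0.955 = 66.8.
- The stated 65 lies within two participants of each. At 65 per group the t-test has 80.8% power.
- Loss to follow-up: 65 / 0.85 = 76.47, matching the stated 76.5.

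The sample size reproduces. It rests on a standardized difference, not on a collapsed table.

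**2. Power lost by ignoring order, analytically.** A one-degree-of-freedom trend test has 80% power when its noncentrality is (1.960 + 0.842)² = 7.85. Give Pearson's test the same noncentrality on k − 1 degrees of freedom:

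| Categories | df | Pearson power | Loss in points |
|---|---|---|---|
| 2 | 1 | 80.0% | 0 |
| 3 | 2 | 70.9% | 9.1 |
| 4 | 3 | 64.5% | 15.5 |
| 5 | 4 | 59.5% | 20.5 |
| 6 | 5 | 55.5% | 24.5 |

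This step needs no assumed score distribution. It assumes that the departure between the arms lies along the trend. The number of categories is not in the document, so the table is a range and not a prediction.

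**3. Simulation check.** Inputs: 65 per group and means 1.4 and 2.3, from the sample size section. The score distribution is an assumption: beta-binomial on 0 to 9 with intra-class correlation 0.15, which gives a standardized difference of 0.51. There were 4,000 simulated trials per setting.

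| Categories | Pearson | Linear trend | Loss in points |
|---|---|---|---|
| 0, 1–2, 3+ | 70.7% | 80.6% | 9.9 |
| 0, 1, 2–3, 4+ | 67.3% | 82.6% | 15.3 |
| 0, 1, 2, 3–4, 5+ | 62.6% | 83.0% | 20.4 |
| 0, 1, 2, 3, 4, 5+ | 58.2% | 82.2% | 24.0 |

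On the uncollapsed score in the same trials, the t-test has 81.2% power and the Mann–Whitney test 83.5%.

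A second set of simulations used 20,000 runs per setting and an assumed SD of 0.9 / 0.5 = 1.8, with beta-binomial and capped negative-binomial shapes. The losses were 8–9, 14–16, 20 and 24–27 points for 3, 4, 5 and 6 categories. With SDs from 1.6 to 2.29 included, the range over 3 to 6 categories was 6 to 27 points.

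**4. Equal average progression, different spread.**

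- A deliberately extreme three-category case, scored 0, 1, 2, has proportions (0.30, 0.40, 0.30) in one arm and (0.40, 0.20, 0.40) in the other. Both means are 1.0. With 65 per arm, Pearson's noncentrality is 65 × (0.01/0.70 + 0.04/0.60 + 0.01/0.70) = 6.19. In simulation it rejects 61% of the time and the trend test 5%.
- A milder case on the 0 to 9 score has means of 1.85 in both arms and intra-class correlations of 0.10 and 0.20 (both assumed). Pearson rejects in 19.1%, 20.2% and 19.8% of trials with 3, 4 and 5 categories. The trend test rejects in 10.2%, 8.5% and 7.2%, and the t-test on the full score in 5.0%.
- With identical distributions in the two arms, all the tests reject in 4.4% to 5.9% of trials.

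**The case against.** The strongest reply is that little hangs on this test. The plan says only that the score may also be collapsed. The t-test or Mann–Whitney test comes first and uses the order. A reader might infer that the trial itself gives up 9 to 24 points of power on the score it was sized on. The document does not support that: the comparison of the full score keeps about 80%, and the 65 per group does not depend on the collapsed analysis. This part of the objection stands and limits the point to a minor one.

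Second, the text does not say Pearson, and a chi-square test for trend is not excluded. A statistical analysis plan that is not shown may settle the form and the categories. This stands in part. The unqualified name is normally read as Pearson's test, and the same section uses chi-square in that unqualified way for retention and demographic data. The point is not that detail is missing, but that the test named does not fit ordered categories.

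Third, the loss depends on a number of categories that the document does not give. With two, such as any progression against none, order plays no part and the loss is zero. With six, little has been collapsed at means of 1.4 and 2.3. This stands, and the size is stated conditionally for that reason.

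Fourth, a reader might take rejection at equal means for an inflated type I error. It is not: the null hypothesis of the chi-square test is equal distributions, and in step 4 the distributions differ. The unequal spread is also an assumption. What remains is a risk of interpretation, if such a result were reported as less progression.

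**Conclusion.** The point holds as a minor, conditional one. If the optional collapsed analysis uses three or more categories and the chi-square test is Pearson's, it is a poorer choice than an ordered test on the same table. The loss is about 9, 16, 20 and 24 points of power with 3, 4, 5 and 6 categories where the trend test has 80%. A significant result may also reflect spread rather than less progression. The analytic losses assume a shift along the trend; the simulated ones also assume a shape and SD for the score. Neither the sample size nor the main comparison of the full score is called into question.

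**What to change.** In Statistical methods, qualify the sentence on the collapsed score along these lines: *If the modified WMH change score is collapsed to three or more categories, it will be assessed with a test for linear trend across the ordered categories (Cochran–Armitage / linear-by-linear association), or with a proportional-odds model adjusted for baseline WMH.* The model has the advantage of giving a common odds ratio and of carrying the baseline covariate.

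The cost is one sentence, with no new data, participants or staff. There are two limits. An ordered test is less sensitive to non-monotone differences, which the trial does not ask about. The trend test also keeps some sensitivity to unequal spread: it rejected in about 7% to 10% of the equal-mean trials above, against about 20% for Pearson's test.
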